### Outcome measures

The primary outcome measure is ventilator free days (VFDs). VFDs will be defined as the number of calendar days from the time of initiating unassisted breathing to day 28 after randomization, assuming survival for at least two consecutive calendar days after initiating unassisted breathing and continued unassisted breathing to day 28. If a patient returns to assisted breathing and subsequently achieves unassisted breathing prior to day 28, VFDs are counted from the end of the last period of assisted breathing. If a patient was receiving assisted breathing at day 27 or dies prior to day 28, VFDs will be zero [13]. Unassisted breathing is defined as being extubated with supplemental oxygen or room air; or open T-tube breathing; or tracheostomy mask breathing; or continuous positive airway pressure (CPAP) ≤5 cm H_2_0 without pressure support. Sites are advised that usual CPAP or (BIPAP) Bilevel positive airway pressure solely for sleep-disordered breathing management is not defined as assisted breathing. Patients receiving pressure support via non-invasive ventilation for any other reason will be defined as receiving assisted ventilation. Patients transferred to another hospital or other health care facility will be followed to day 28 to assess this endpoint.

There are a number of secondary outcomes for this clinical trial which include clinical outcomes, safety, health economic evaluation and biological mechanisms.

The secondary clinical outcomes are change in OI from baseline to day 3, 7, 14 and 28; change in SOFA score from baseline to day 3, 7, 14 and 28; non pulmonary organ failure free days (defined as the number of days in the first 28 days after randomization that the patient received no cardiovascular, renal, liver or neurological support as defined by the Critical Care Minimum Dataset [14]); all cause mortality 28 days post randomization; mortality at (first) discharge from critical care; mortality at (first) discharge from hospital and mortality at 12 months post randomization.

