### Power and sample size estimate

The mean (standard deviation; SD) VFDs in 432 patients with ALI was 12.7 (10.6) days [16]. The SD (10.6) for VFDs in ALI used for the sample size calculations is similar to the SD for VFDs that has been consistently reported in other large multi-center clinical trials [17-19]. There are no prospective trials in patients with ALI to predict the treatment effect size of simvastatin to improve VFDs. In a recent retrospective study, statin usage in patients with ALI was associated with a 31% increase in VFDs [20]. Our observational data showed a 37% relative improvement in mortality in patients who received a statin [4]. In our proof of concept study, OI and SOFA scores improved by 50% to 66%, respectively, in the simvastatin-treated group [11]. Pre-treatment with simvastatin decreased a range of pulmonary inflammatory mediators induced by LPS in healthy volunteers by between 34% to 65% [10]. On the basis of these data, a conservative treatment effect of 20% has been estimated for this study.

A sample size of 524 subjects (262 in each group) will have 80% power at a two-tailed significance level of 0.05 to detect a 20% difference in VFDs. To estimate loss after recruitment, previous data from the PAC-Man trial were used where 2.4% of recruited patients or their relatives subsequently withdrew their consent, or were randomized in error [21]. Thus, estimating a dropout rate of 3% the study will require a total of 540 patients with 270 in each group (Figure 1).

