### Randomization and study drug supply

Patient drug packs will be prepared by Victoria Pharmaceuticals (Belfast, UK). Simvastatin 40 mg or identical placebo tablets will be packaged in a white opaque plastic container which will be sealed with a tamper-evident seal and labelled in compliance with applicable regulatory requirements. Each container will contain 70 tablets of the study drug for the treatment of one patient for 28 days (plus 7 days overage). All trial drugs will be packaged identically and identified only by the unique trial identifier.

Patients will be randomized in a 1:1 ratio using an automated centralized 24-hour telephone or web-based randomization service (Centre for Healthcare Randomised Trials, University of Aberdeen, UK). Randomization will be stratified by site and by vasopressor requirement (defined as any inotropic requirement except dopamine <6 mcg/kg/minute). The randomization service will allocate a unique trial identifier to each patient in accordance with the computer-generated study randomization schedule. The randomization service will confirm randomization details by email to the CTU and the study site. A confirmation email will be sent to the hospital pharmacy. The clinician will complete a trial prescription form detailing the unique trial identifier assigned to the patient. The hospital pharmacy will dispense the drug pack labelled with the corresponding unique trial identifier for the patient.

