### Statistical analysis plan

Standard approaches will be used to detect patterns in missing data. Analyses will be on an intention-to-treat basis. As VFDs are unlikely to be normally distributed, the groups will be analyzed by comparing the medians and 95% confidence intervals (CI). The comparison of other continuous outcomes will be by analysis of variance, including covariates where appropriate. Statistical diagnostic methods will be used to check for violations of the assumptions, and transformations will be performed where required. A statistical interaction test will be used to assess differences in treatment effects between the subgroups. For binary outcome measures risk ratios and associated 95% CI will be calculated. Binary variables assessed daily will be analyzed using logistic regression analysis corrected for days at risk. Time-to-event outcomes will be analyzed by survival methods and reported as hazard ratios with 95% CI. An interim analysis of efficacy is not planned.

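### The stated primary analysis compares VFD medians between arms without the stratification factors, so some precision may be forgone

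*Protocol article*

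**What the plan says.** Under Outcome measures: "The primary outcome measure is ventilator free days (VFDs"). Under Randomization and study drug supply: "Randomization will be stratified by site and by vasopressor requirement"; the Abstract gives the same two factors.

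Under Statistical analysis plan, the VFD method follows from the expected non-normality of the outcome: "the groups will be analyzed by comparing the medians and 95% confidence intervals (CI"). The next sentence reads: "The comparison of other continuous outcomes will be by analysis of variance, including covariates where appropriate". Neither stratification factor is named in that section. Vasopressor requirement returns under Subgroup analyses as a possible effect modifier. That tests an interaction and does not adjust the main comparison. The same section says that a detailed SAP has been written; it is not shown.

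Under Power and sample size estimate, the inputs are "The mean (standard deviation; SD) VFDs in 432 patients with ALI was 12.7 (10.6) days" and a 20% difference. The SD is used in full, with no reduction for stratification.

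**The concern.** Stratified allocation balances site and vasopressor requirement between the arms. If these factors predict VFDs, the balance lowers the true sampling variance of the treatment contrast. An analysis that omits them still estimates its standard error from the whole spread of the outcome, including the between-stratum part that the design has removed from the contrast. The standard error is then too large, the 95% interval covers more than 95% of the time, and the test rejects less often than its nominal level.

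The article names a primary method with no adjustment and mentions covariates immediately afterwards for the other continuous outcomes. The natural reading is a plain two-group contrast on the outcome for which precision matters most. At stake is precision on the primary endpoint, not validity.

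**Working it through.** **Inputs from the article (Power and sample size estimate).** Mean VFDs 12.7, SD 10.6; effect 20%; "will have 80% power at a two-tailed significance level of 0.05"; "A sample size of 524 subjects (262 in each group"). The difference in days is not printed; 0.20 × 12.7 = 2.54.

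**Assumed input.** R², the share of VFD variance explained by site and vasopressor requirement together. The article gives no figure, so a range of 0 to 20% is used.

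**Step 1: the plan's own figure.** For two means, n per group = 2(z₀.₉₇₅ + z₀.₈₀)² SD²/δ² = 2 × (1.960 + 0.842)² × 10.6²/2.54² = 273.4, so 274 per group (548 in total). The printed figure is 262 per group (524). A difference rounded to 2.6 days gives 261 (normal approximation) or 262 (t-test), so rounding probably explains it. At 262 per group and 2.54 days, SE = 10.6 × √(2/262) = 0.926, 2.54/0.926 = 2.743, and power = Φ(2.743 − 1.960) = 78.3%. This shortfall is a separate matter from stratification.

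**Step 2: effect of using or ignoring the factors**, assuming near-perfect balance.
- Adjusted power: Φ(2.743/√(1 − R²) − 1.960).
- Unadjusted power: the true SE is 0.926√(1 − R²) but the analysis uses 0.926, so power = Φ((2.743 − 1.960)/√(1 − R²)).
- Unadjusted two-sided type I error: 2[1 − Φ(1.960/√(1 − R²))].
- Unadjusted interval width relative to adjusted: 1/√(1 − R²).

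| Assumed R² | Adjusted power | Unadjusted power | Unadjusted type I error | Width ratio |
|---|---|---|---|---|
| 0% | 78.3% | 78.3% | 5.0% | 1.00 |
| 2% | 79.1% | 78.5% | 4.8% | 1.01 |
| 5% | 80.3% | 78.9% | 4.4% | 1.03 |
| 10% | 82.4% | 79.5% | 3.9% | 1.05 |
| 15% | 84.5% | 80.2% | 3.4% | 1.08 |
| 20% | 86.6% | 80.9% | 2.8% | 1.12 |

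As an example, at R² = 10%, √0.9 = 0.949. Adjusted power is Φ(2.891 − 1.960) = Φ(0.931) = 82.4%; unadjusted power is Φ(0.783/0.949) = Φ(0.825) = 79.5%.

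**Step 3: check with imperfect balance and many sites.** A simulation assumed 35 sites, two equal vasopressor strata, blocks of four, a normal outcome, N = 524 and 3,000 runs per setting. It compared linear models with and without fixed site and vasopressor effects. The Monte Carlo error on power is about 0.7 points.

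| Assumed R² | Power, unadjusted | Power, adjusted | Type I, unadjusted | Type I, adjusted |
|---|---|---|---|---|
| 0% | 79.0% | 78.6% | 5.1% | 5.1% |
| 5% | 78.1% | 78.7% | 4.5% | 4.9% |
| 10% | 79.6% | 82.1% | 4.4% | 5.6% |
| 15% | 80.1% | 84.0% | 3.9% | 5.2% |

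The direction agrees with Step 2. At R² = 5% the power gain cannot be distinguished from simulation noise.

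**Step 4: what such an R² would require.** For vasopressor requirement alone, R² = p(1 − p)D²/SD², where p is the proportion on vasopressors and D the difference in mean VFDs between strata. With p = 0.5 (assumed), D = 2, 4 and 6 days gives 0.9%, 3.6% and 8.0%. A total of 10% therefore needs a strong vasopressor effect, a real contribution from site, or both.

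All these figures concern means. The article gives no distribution from which the power of a median comparison could be computed.

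**The case against.** The strongest objection is that the article never says the primary comparison is unadjusted. It is a condensed account, it refers to a detailed SAP, and the list of model terms is commonly left to that document. Much of this stands: the SAP may already include both factors, and confidence should be moderate. It does not remove the point. The article goes beyond silence: it names the primary method and places covariates with the other continuous outcomes. A reader is given an analysis that does not match the randomization.

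It can also be objected that the loss is small, the direction is conservative, and power gains for means need not carry over to medians. All of that is correct and limits the size of the point.

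Three stronger inferences are not supported:
- **That planned power is being thrown away.** The sample size rests on the full SD of 10.6 and counts on no gain from stratification. What is forgone is extra precision.
- **That factors explaining 5% of variance would bring power back to the stated 80%.** The formula gives 80.3%, but the simulation gives 78.7% adjusted against 78.1% unadjusted.
- **That the mortality risk ratios are stated as unadjusted.** The article says only that risk ratios with intervals will be calculated, and a risk ratio can be adjusted.

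**Conclusion.** The point holds in a limited form. As written, the primary VFD analysis does not use the factors on which allocation was stratified. If they are prognostic, the interval is too wide (about 3%, 5% and 8% at assumed R² of 5%, 10% and 15%) and the test is conservative. The power forgone is about 1.4, 2.9 and 4.3 points at those values by formula, and negligible at 5% or below. The estimate is not biased, and power does not fall below plan for this reason.

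The figures rest on an R² that the article does not supply, on near-perfect balance, and on a comparison of means standing in for one of medians. The conclusion also depends on the unseen SAP not already specifying the adjustment.

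**What to change.** State that the primary VFD comparison accounts for vasopressor requirement and site, using a method suited to the non-normal outcome. Two options are a rank test stratified by these factors, or median (quantile) regression with both as covariates. A rank test alone gives no median difference, so the source of the estimate and its interval should be named too. Median regression gives a difference in medians conditional on the factors. Reporting the unadjusted median comparison as supportive keeps the comparison that the article describes.

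Prespecify how site enters. With 540 patients and about 35 ICUs the average is 540/35 ≈ 15 per site, and about 540/70 ≈ 8 per site-by-vasopressor stratum, so a rule for pooling small sites is needed. Confirm that the SAP says the same.

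The cost is a short addition to the text and slightly more analysis work. No new data are needed, since both factors must be known to randomize a patient. The article reports recruitment still under way and no planned interim efficacy analysis, so at that stage the choice could be fixed before any comparative result is seen.

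### The primary VFD comparison is described without covariates; pre-specified adjustment for age, baseline OI and baseline SOFA could add precision at no recruitment cost

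*Protocol article*

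**What the plan says.** The Statistical analysis plan section of the protocol article assigns a method to each class of outcome.

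- **VFDs (primary):** the groups are compared by medians with 95% confidence intervals, because a normal distribution is not expected. No covariate is named.
- **Remaining continuous outcomes:** "The comparison of other continuous outcomes will be by analysis of variance, including covariates where appropriate". The covariates are not listed.
- **Binary outcomes, which include the mortality endpoints:** "For binary outcome measures risk ratios and associated 95% CI will be calculated". Nothing is said about adjustment in either direction.
- **Binary variables assessed daily:** logistic regression with a correction for days at risk.

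Three baseline measures are available without new data collection. Outcome measures lists "change in SOFA score from baseline to day 3, 7, 14 and 28" and the same change for OI, and both need a baseline value. Age is a planned subgroup factor (Subgroup analyses). Randomization is stratified by site and vasopressor requirement (Randomization and study drug supply), and the analysis section does not mention either factor as a covariate.

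The Subgroup analyses section says that a detailed SAP has been written. It is not available here.

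**The concern.** The text sets VFDs apart from the one class of outcome that is given covariates, and the method it names for them, a two-group comparison of medians, has no covariate term. Read as written, the primary analysis is unadjusted.

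Age, OI and SOFA describe how ill a patient is at entry, so it is reasonable to expect them to carry some information about VFDs. A patient who dies before day 28 scores zero, so anything that predicts death also predicts the primary outcome. The article itself does not quantify this link. To the extent that it exists, an unadjusted analysis leaves explainable variation in the error term and gives a wider interval than the same patients could provide. The same reasoning applies to the mortality risk ratios, with the difference that the text there is silent and names no method that excludes covariates.

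What is at stake is efficiency. The validity of the comparison is not in question.

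**Working it through.** **Inputs** (Power and sample size estimate)

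- Mean and SD of VFDs: "The mean (standard deviation; SD) VFDs in 432 patients with ALI was 12.7 (10.6) days".
- Effect: "a conservative treatment effect of 20% has been estimated for this study", so the difference is 0.20 × 12.7 = 2.54 days.
- Size: "A sample size of 524 subjects (262 in each group) will have 80% power at a two-tailed significance level of 0.05".
- R², the share of VFD variance explained by age, baseline OI and baseline SOFA together: not in the document. Assumed range 0.05 to 0.20.

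**Step 1. Reproduce the plan's figure.** For two means, n per group = 2 (1.96 + 0.84)² SD² / difference².

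- With 2.54 days: 274 per group, 548 in total. At the stated 262 per group, power is 78.3% by the normal approximation and 78.2% by the noncentral t with 522 degrees of freedom.
- With the difference rounded to 2.6 days: 261 per group (normal) or 262 (t test), which matches the stated size. Power at 262 is then 80.0% (t).

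The stated size therefore reproduces as a comparison of means with the unadjusted SD of 10.6. It makes no use of covariates.

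**Step 2. Effect of adjustment on the mean scale.** The residual SD is 10.6 × √(1 − R²) and the standard error of the difference is residual SD × √(2/262). The unadjusted sample that would give the same precision is 262 / (1 − R²) per group. Power is from the noncentral t with 522 degrees of freedom; the few degrees of freedom used by three covariates make no visible difference.

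| R² | Residual SD | SE (days) | Power, 2.54 days | Power, 2.6 days | Equivalent n per group | Interval narrower by |
|---|---|---|---|---|---|---|
| 0 | 10.60 | 0.926 | 0.782 | 0.800 | 262 | – |
| 0.02 | 10.49 | 0.917 | 0.790 | 0.808 | 267 | 1.0% |
| 0.05 | 10.33 | 0.903 | 0.802 | 0.820 | 276 | 2.5% |
| 0.10 | 10.06 | 0.879 | 0.823 | 0.840 | 291 | 5.1% |
| 0.15 | 9.77 | 0.854 | 0.844 | 0.860 | 308 | 7.8% |
| 0.20 | 9.48 | 0.828 | 0.8645 | 0.880 | 328 | 10.6% |

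The row at 0.02 shows that the gain is small when the covariates explain little. The column for 2.6 days shows that the gain does not depend on how the 20% effect was rounded.

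**Step 3. Mortality, as an illustration.** The Background gives mortality of about 30% to 40%. Assume a risk ratio of 0.8, 262 per group, and adjustment that acts like dividing n by (1 − R²).

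| Control mortality | R² = 0 | R² = 0.10 | R² = 0.20 |
|---|---|---|---|
| 30% | 34% | 37% | 41% |
| 35% | 41% | 44% | 49% |
| 40% | 48% | 52% | 57% |

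The risk ratio and R² are both assumptions. The article states no power target for mortality, so the table shows only the likely order of the gain.

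**Limit of the check.** Steps 1 and 2 concern a difference in means. The planned analysis compares medians, and the variance reduction from covariates does not carry over directly to that estimator.

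**The case against.** The strongest reply is that this belongs in the SAP. A journal article condenses the plan, the article says that a detailed SAP exists, and a list of covariates is commonly left to it. That would answer a complaint that the list is missing. It answers this point only in part, because the article does name a method for the primary outcome and that method is unadjusted. Either the SAP adjusts and the article does not describe it, or the SAP follows the article and the precision is forgone.

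Other objections stand, and they limit the point:

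- **A reader might infer that the plan forbids covariates for mortality.** It does not. The sentence on risk ratios is silent, and a risk ratio can be adjusted.
- **A reader might infer that the trial needs this precision to reach its power.** The document does not support that. The trial was sized on the unadjusted SD. With the literal 2.54 days the gap to 80% is under two percentage points, and it disappears with rounding to 2.6 days.
- **A reader might infer that chance imbalance in severity biases the result.** An unadjusted randomized comparison is valid and its interval already allows for chance imbalance. Stratification by vasopressor requirement also balances one marker of severity.
- **R² is not in the document**, and no section shows how strongly these variables predict VFDs.
- **An adjusted mean difference is a different estimand from a difference in medians.** It should be added openly as such, and the model should include the stratification factors.

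**Conclusion.** The point holds as one of efficiency. The article describes the primary VFD comparison as unadjusted, names covariates only for the remaining continuous outcomes, and is silent on adjustment for binary outcomes, although three plausible prognostic measures are already collected.

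On the mean scale used for the sample size, with 262 per group, SD 10.6 and 2.54 days, adjustment would raise power from about 78% to between 80% and 86%, and narrow the interval by about 3% to 11%. This rests on an assumed R² of 0.05 to 0.20; at 0.02 power would be about 79%. The figures describe a mean difference and not the planned comparison of medians. The planned analysis is not wrong, and the document does not show that the trial fails without the change.

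**What to change.** Before unblinding, in the SAP and in the article's Statistical analysis plan section:

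1. Pre-specify a covariate-adjusted VFD effect as a mean difference, which is the scale on which the trial was powered. Use regression on treatment, age, baseline OI, baseline SOFA, vasopressor requirement and site, with robust or bootstrap standard errors.
2. Keep the planned unadjusted median comparison and report it alongside. State in advance which of the two carries the primary conclusion.
3. Estimate mortality risk ratios by standardized logistic or modified Poisson regression with the same covariates, and report the unadjusted ratios as sensitivity analyses.
4. State how site enters each model. With 540 patients in about 35 units there are about 15 patients per site (540 / 35 = 15.4), so small sites may need pooling or a random effect.
5. Fix the covariate list, the form of each covariate and a simple rule for imputing missing baseline values.
6. If the SAP already adjusts these analyses, change the article's text to agree with it.

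The cost is SAP wording and some programming, with no new data and no extra patients. The price is a covariate list that cannot be changed later, imputation of any missing baseline values (probably few), and a mean-scale result that has to be explained next to the medians. The article reports 293 patients enrolled as of December 2012 in a blinded trial with no interim efficacy analysis planned, so at that stage the list could still be fixed without knowledge of results by arm.

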### Subgroup analyses

Four subgroup analyses are planned to analyze whether treatment effect is modified by age, vasopressor requirement (defined as any inotropic requirement except dopamine <6mcg/kg/minute); etiology of ALI (due to sepsis versus non-sepsis) and CRP level at baseline. Subgroup analyses will use a statistical test for interaction and will be reported using 99% CI. The trial statistician has written a detailed statistical analysis plan (SAP).

